## Abstract

**Background:**

The negative emotional valence of a stimulus can be altered if paired with a pleasant stimulus, a phenomenon referred to as evaluative conditioning. Disgust, as a central emotion in obsessive-compulsive disorder (OCD), particularly in the contamination subtype, may be an appropriate target for such a method. We know that disgust processing and OCD pathophysiology share in some brain areas, including the orbitofrontal cortex, as the neuromodulation techniques targeted in this area have been able to decrease OCD symptoms. We aim to conduct a randomized clinical trial to investigate the evaluative conditioning effect on disgust reduction in patients with contamination-based OCD when administered with or without neuromodulation targeted orbitofrontal cortex.

**Method:**

In a single-blind randomized control trial (RCT), 55 patients with contamination-based OCD will be randomly assigned to four arms. In a factorial design, they will receive 10 sessions of evaluative conditioning training (either sham or real) plus cathodal transcranial direct current stimulation (tDCS) over the orbitofrontal cortex (either sham or real). The intensity of disgust experience and clinical symptoms will be investigated as primary outcomes and quantitative electroencephalogram and cognitive functions as secondary outcomes. The data will be collected at three assessment levels: baseline, after completing intervention sessions, and 2-month follow-up.

**Discussion:**

The present RCT is the first study that applies evaluative conditioning training in the OCD clinical sample. It will clarify the effect of the evaluative conditioning method alone and with tDCS on disgust reduction in patients with contamination-based OCD. It will provide initial evidence for such an emotion modulation method in the OCD population. The effect of this emotion-focused protocol on cognitive functions and electroencephalogram components is also of interest.

**Trial registration:**

ClinicalTrials.gov, NCT05907369. Registered on 16 June 2023. Retrospectively registered.

**Supplementary Information:**

The online version contains supplementary material available at 10.1186/s13063-023-07791-2.

## Background

Obsessive-compulsive disorder (OCD) is a disabling mental with a lifetime prevalence of 2–3% [1, 2]. It is known by repetitive, unwanted, persistent thoughts, images, or urges as obsessions and repetitive behaviors or mental rituals as compulsions. It reduces the quality of life since it is accompanied by cognitive, social, and occupational deficits [3, 4]. Considering the symptom diversity, nearly half of OCD patients are concerned about dirt, germs, affections, and diseases, accompanied mainly by excessive washing and cleaning behaviors [5], called contamination-based OCD (C-OCD). It has become more critical since a considerable increase in C-OCD prevalence has occurred in recent years due to the COVID-19 pandemic [6, 7].

It is believed that disgust is an essential emotional characteristic of OCD and has a central role in the development, maintenance, and treatment of the disorder [8], particularly in C-OCD, so Curtis [9] claimed that “the disorder of disgust system” is a more appropriate description for this mental condition. Disgust showed a stronger correlation with contamination symptoms [10, 11]. Supposed that the functional role of disgust is to keep us away from dirt and diseases, C-OCD seems to be an exaggerated disgust processing, including a false contamination alarm that resulted in excessive avoidant behavior. The C-OCD sufferers experience abnormal mental contamination, meaning they feel contaminated despite no physical contact with an actual contaminant [12]. Dysfunctional disgust processing is the culprit for such a false contamination alarm [8].

There are a growing number of studies that targeted disgust in OCD. For example, Fink et al. [13] reduced disgust in C-OCD patients through two emotion-regulation techniques: imagery rescripting and cognitive reappraisal. Other methods are also administered to reduce disgust, such as exposure-based cognitive-behavioral therapy [14], imagery rescripting combined with brain stimulation [15], and virtual reality (VR) exposure [16]. Disgust reduction corresponds with improvements in C-OCD symptoms [14, 17], and disgust proneness (i.e., how much one is prone to experience disgust) is associated with treatment results [18, 19]. It also showed an association with treatment results at the follow-up level [20].

In the recent book on disgust, Reynolds and Askew concluded that disgust is mainly developed through evaluative conditioning (EC) [21]. EC is a process through which pairing a neutral-valence stimulus (conditioned stimulus; CS) with an emotional-valence stimulus (unconditioned stimulus; US) could result in a change in the emotional valence of the CS. So, it can change the amount of liking or disliking of the target stimulus (i.e., CS). The change is referred to as the “EC effect.” EC is resistant to extinction [22] because extinction does not target the valence of CS. Therefore, extinction may not appropriately reduce disgust emotion [23].

Although exposure-response prevention (ERP) is the first-line behavioral treatment for OCD, there are inconsistencies in the effectiveness of exposure-only to reducing disgust [20, 24]. The exposure-only technique seems successful in reducing fear rather than disgust. It may be due to the role of Pavlovian conditioning in producing fear responses and its sensitivity to the extinction phenomenon, compared with the role of evaluative conditioning in disgust reactions and its resistance to extinction [25]. Disgust resistance to extinction is an important obstacle toward treatment, particularly for those with higher disgust proneness [23]. C-OCD patients, compared with other OCD subtypes, experience higher levels of disgust and move more slowly through the habituation process in the ERP interventions [26].

Another method known as counterconditioning may be effective in modifying CSs with disgust valence. In counterconditioning, a CS is paired with a US with opposite valence. Pairing disgusting stimuli with pleasant USs seems to be a preferred treatment approach for reducing disgust even in OCD patients [24, 25]. Evaluative counterconditioning has led to a decrease in disgust valence in OCD analog samples with contamination concern [27] and in other disgust-relevant conditions like body dissatisfaction [28]. Considering the central role of disgust in C-OCD, EC may have therapeutic implications for clinical OCD populations, but the effectiveness for the OCD population has remained unclear.

OCD pathophysiology shares neurocircuits and brain structures involved in disgust processing [29]. Among them are the insular cortex and orbitofrontal cortex (OFC). Insular activity is a neural correlate for disgust processing [30, 31]. Insula shows regular higher activity in experiencing actual disgusting stimuli, but the abnormality is when an OCD patient confronts a symptom-provoking stimulus that is not genuinely disgusting. In this situation, insular hyperactivity showed that non-disgusting stimuli are mistakenly perceived as highly disgusting [32]. The insula sends some projections to the OFC [33, 34], the area engaged in coding the aversive value of the stimuli [35], and its enhanced activity, among the insula and other areas, is associated with avoidance behavior in a disgust-relevant situation [36]. The OFC also showed increased gray matter volume in people with higher disgust sensitivity (how much they are distressed when experiencing disgust) [37]. Neuroimaging studies reported the overactivation of OFC in OCD patients [38]. The neuromodulation techniques in this area, such as transcranial direct current stimulation (tDCS), have a therapeutic effect on OCD symptoms [39, 40].

The present study aims to design an EC training targeting disgust toward contamination-related stimuli in C-OCD patients. The hypothesis is that pairing such stimuli with pleasant USs may decline the disgust evoked. The proposed intervention will target lings of disgust more directly and precisely. We will also investigate the effect of brain stimulation over the OFC on disgust processing in C-OCD people. Finally, we are interested in whether adding this neuromodulation technique to the EC training may boost the EC effect. So, we will compare the effectiveness of individual and combined interventions in reducing disgust reactivity.

We hypothesize that EC and brain stimulation would decrease disgust experience when exposed to contamination-related stimuli (primary outcome), which, in turn, would improve OCD symptoms (primary outcome). Moreover, since emotional processing can interfere with cognitive functions [41], it is hypothesized that decreases in disgust reactivity would be associated with increases in cognitive functions, particularly in one’s disgust-related attentional bias and inhibitory control (secondary outcomes). We will use electroencephalographic (EEG) characteristics to examine the effectiveness of EC, brain stimulation, and their combined use combination of the (secondary outcome).

Below is a detailed description of the proposed randomized control trial (RCT) following the SPIRIT framework [42].

## Methods/design

### Study design and setting

This study is a four-arm, randomized, placebo-controlled clinical trial in which participants get sham or real forms of two interventions, including EC and tDCS. It is aimed to investigate the effectiveness of EC, tDCS, and a combination of both on disgust reduction, clinical symptoms, and cognitive characteristics in C-OCD patients. Randomly assignment will be in blocks of 4 in 1:1:1:1 allocation to four parallel groups: (1) real EC plus real tDCS, (2) sham EC plus real tDCS, (3) real EC plus sham tDCS, (4) sham EC plus sham tDCS. We consider sham interventions to be able to separate the exposure effect from the EC effect and also to monitor the placebo effect. Assessments occur at baseline, after completion of 10 interventional sessions, and in a 2-month follow-up. All groups have similar assessments and equal intervention amounts (equal time, activity, and number of sessions). Figure 1 shows the design of the study. The trial will be conducted in the Cognitive Science Laboratory of Ferdowsi University of Mashhad, Mashhad, Iran.

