##### Real tDCS

Stimulation will be provided using the standard device (Activadose DC stimulator) with two rectangular saline-soaked sponge electrodes placed based on the international 10-20 electrode placement system. The cathode (size 5 × 7 cm^2^) will be placed over the left OFC (FP1) and the anode (size 10 × 10 cm^2^) over the right cerebellum (3 cm below the inion and 1 cm right of the midline). This montage is similar to that of Bation et al. [39], but increasing the size of the reference electrode (anode) is due to have a more focal cathodal effect over the left OFC. The tDCS will be delivered with the current intensity of 2 mA for 20 min for 10 sessions (5 days a week).

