**Table 1 Tab1:**
[figure not shown]
Procedure schedule

*EC*, evaluative conditioning, *tDCS*, transcranial direct current stimulation, *EEG*, electroencephalography, *DPT*, dot-probe test, *EGNT*, Emotional Go/NoGo test, *ESST*, Emotional Stop-Signal test, *PI-WSUR*, Padua Inventory-Washington State University Revision, *Y-BOCS*, Yale-Brown Obsessive-Compulsive Scale, *DS-R*, Disgust Scale-Revised, *BDI-II*, Beck Depression Inventory-II, *BAI*, Beck Anxiety Inventory, *DRS*, Disgust Rating Scale

The primary outcome measures will be disgust reduction and change in clinical symptoms. We hypothesize that pairing C-OCD-related stimuli with positive USs can reduce disgust feeling toward them in C-OCD patients, and simultaneously cathodal tDCS over left OFC may boost this effect. For that, we will measure the amount of disgust elicited by contaminated stimuli on a Disgust Rating Scale, at baseline and after completing interventions. We will also look for possible transfer effects in OCD symptoms from pre- to post-interventions, measured via PI-WSUR and Y-BOCS. Based on previous studies in which the role of disgust has been implied in the pathology of OCD and the assumption that targeting this negative emotion may have treatment outcomes, it is hypothesized that EC may lead to diminishing C-OCD symptoms, mainly when it is along with cathodal tDCS, over left OFC.

The secondary outcomes include cognitive measures and QEEG recording. Disgust as a negative emotion may affect cognitive functions [61, 62], and OCD patient has been shown to have cognitive deficits in attention, memory, and executive function [63–65]. First, we aim to examine attentional bias and inhibitory control in C-OCD patients when confronted with contaminated stimuli compared with neutral ones. Then, the study will explore whether entering these contaminated stimuli into a positive EC training leads to better performance in these cognitive tests. We are also interested in investigating the correlation of cognitive performance level with the self-reported disgust rating, both at the baseline and after completing interventions. For QEEG recording, we will look for changes in brain wave characteristics from pre- to post-interventions.

We expect a more significant effect for all measures when the EC training is combined with cathodal tDCS than each one alone. We will also detect hypothesized effects at a 2-month follow-up.

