### Sample size

We calculated the sample size using the G*Power 3.1 software. To be able to get an effect on our primary outcomes (disgust feeling and clinical symptoms) in three measurements (pre-, post-, and follow-up) at repeated-measure-MANOVA approach, with 95% confidence and 80% power, estimating large effect size with Cohen’s *f* value 0.40, a sample size of 46 participants was calculated. With an attrition rate of 20%, we aim to enroll 55 participants.

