### Statistical analysis

First, data entry will be double-checked. Data quality will be examined regarding data distribution, and outliers will be excluded from further analysis. When these items are ensured, the primary and secondary outcomes will be analyzed in detail using IBM SPSS statistics 25 for Windows (Armonk, NY: IBM Corp). Descriptive statistics (e.g., mean and standard deviation) will be reported for each arm separately. We will conduct the analysis within the intention-to-treat (ITT) framework to investigate the effectiveness of the interventions for all subjects with multiple imputed data sets in case of missing data. The appropriate statistical method will be performed to analyze data. The major one will include mixed and repeated measures of multivariate analysis of variance (MANOVA) to assess the effect of group (arm) and time and their interactions on the result of EEG recordings, computerized tests, and self-report measures as dependent variables. The significant level will be set at 0.05. The covariates, including age, disgust sensitivity, anxiety, and depression, will be considered in the statistical model.

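### Outcome collection depends on staying on the intervention: participants who stop early have no post-treatment assessment date in the visible text, while the analysis promises intention to treat for all subjects

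*Protocol article*

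**What the plan says.** Under Study design and setting, the schedule reads: "Assessments occur at baseline, after completion of 10 interventional sessions, and in a 2-month follow-up". The abstract repeats it: "baseline, after completing intervention sessions, and 2-month follow-up". Under Expected outcomes, the primary disgust measure is taken "on a Disgust Rating Scale, at baseline and after completing interventions". The visible text sets no window counted from randomisation or first session, and no start date for the two months of follow-up. The Real tDCS section plans ten sessions at five days a week. The Procedure section takes it that every participant will finish all ten.

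Two passages deal with participants who do not follow that course. Adverse effect monitoring says that if a participant reports a moderate to serious problem, stimulation stops and the trial ends for that person. Participants says that anyone who receives a new prescription or other brain stimulation during the trial or follow-up is left out of later assessments or of the analysis.

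Statistical analysis then says: "We will conduct the analysis within the intention-to-treat (ITT) framework to investigate the effectiveness of the interventions for all subjects", continuing "with multiple imputed data sets in case of missing data". Sample size says: "With an attrition rate of 20%, we aim to enroll 55 participants".

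**The concern.** An intention-to-treat analysis needs outcomes from everyone randomised, including those who stopped treatment. Here the assessment follows the last session, so a participant who leaves after session 6, for example, has no assessment falling due under the visible text. Stopping treatment then produces a missing outcome even when the participant would willingly fill in a short questionnaire.

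Such losses may be related to outcome and to arm. Real stimulation is 2 mA and sham is 0.1 mA, and real training uses pleasant pictures where sham uses neutral shapes, so tolerance could differ. The article gives no dropout by arm, so this is a risk and not a shown fact.

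Imputation can be specified later in an analysis plan, but it cannot recover outcomes that were never collected.

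**Working it through.** **1. The passages side by side.**
- Timing (abstract, Study design and setting, Expected outcomes): the assessment follows completion of the sessions.
- Adverse effect monitoring: the trial ends for some randomised participants, and no later assessment is mentioned.
- Participants: some randomised participants are dropped from assessments or analysis.
- Adherence and retention: covers commitment and reminders, and does not mention assessment after stopping.
- Statistical analysis: effectiveness in all subjects.

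The first four do not supply the data that the fifth needs. The Participants rule contradicts it directly, because it removes randomised people from the analysis.

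**2. The plan's own sample size.** Inputs from Sample size and Study design: f = 0.40, alpha 0.05, power 80%, 4 arms, 3 measurements. For the repeated-measures MANOVA group-by-time interaction (Pillai), s = 2, df1 = 3 × 2 = 6, df2 = 2(N − 4) and noncentrality = f² × s × N. At N = 46, df2 = 84, noncentrality = 0.16 × 2 × 46 = 14.72 and power = 0.802. The stated 46 is reproduced. The 55 matches 46 × 1.2 = 55.2, rounded down. (Dividing 46 by 0.8 gives 57.5, so 58; that is a separate matter.)

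**3. How many could be affected.** 0.20 × 55 = 11, or 11/4 = 2.75 per arm of 55/4 = 13.75. This leaves 44 with an observed post value. It is a ceiling, because it counts all attrition as early stopping.

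**4. Power at the full effect, same formula.**
- 44 observed: noncentrality 14.08, df2 = 80, power 0.779.
- 55 observed: noncentrality 17.60, df2 = 102, power 0.882.

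**5. If stoppers keep only part of the benefit.** Assumption, not in the article: 20% stop and keep a share q of the effect, so f = 0.40 × (0.8 + 0.2q).

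| Share kept (q) | f | Power, all 55 assessed |
|---|---|---|
| 100% | 0.40 | 0.88 |
| 75% | 0.38 | 0.84 |
| 50% | 0.36 | 0.79 |
| 25% | 0.34 | 0.74 |
| 0% | 0.32 | 0.67 |

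Measuring everyone does not always raise power above the 0.779 available with 44. When stoppers keep little benefit, the all-subjects effect is smaller. That smaller effect is nevertheless the one the plan says it will estimate.

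**6. Bound on overstatement.** If imputation gave stoppers the completers' full effect, the estimate would exceed the all-subjects effect by 1/[1 − p(1 − q)] − 1, where p is the share who stop.
- p = 0.20, q = 0: 1/0.80 − 1 = 25%.
- p = 0.20, q = 0.5: 1/0.90 − 1 = 11%.
- p = 0.10, q = 0: 1/0.90 − 1 = 11%.

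The first is a worst case.

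**The case against.** The strongest reply is that the timing phrase simply describes the planned course. No sentence says that early stoppers go unassessed. Table 1, to which the article refers for its time points, and Figure 1 cannot be seen here, and an article commonly leaves visit windows to the full protocol. An end-of-treatment assessment is a normal choice for a short course. Much of this stands: the timing phrase alone would justify no more than a request for clarification. What it does not answer is the pair of rules under Participants and Adverse effect monitoring. These are positive statements that end assessment, analysis or trial participation for some randomised people, and they conflict with an analysis of all subjects.

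A reader might go further and infer that the intention-to-treat result becomes a completers' result. The article does not support that. It promises imputation, which keeps every subject in the analysis and can draw on baseline scores and on the listed covariates (age, disgust sensitivity, anxiety, depression).

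A reader might also infer that anyone who misses sessions never reaches the post assessment. Such a participant may simply finish later, in which case the assessment date moves but is not lost.

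Nor can the whole 20% allowance be read as missing post values. It may include losses during the two-month follow-up, after the post assessment has been done, and exclusions under the Participants rule.

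**Conclusion.** The point holds in a limited form. As written, outcome collection depends on remaining on the intervention, and two stated rules stop assessment, analysis or participation for some randomised participants, while the analysis is promised for all. The estimate for early stoppers would then rest mainly on completers' data under a missing-at-random assumption; the article names no other.

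The size is at most about 11 of 55, if all of the stated attrition is early stopping. The 25% overstatement needs that full 20%, no retained benefit in any stopper, and imputation that corrects nothing. It is an outer bound and not an expected value. The conclusion also assumes that the unseen table, flow chart and full protocol do not already schedule assessments for those who stop.

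**What to change.** Keep the end-of-treatment assessment for participants who complete the ten sessions. For anyone who stops early, or who falls under the rules in Participants or Adverse effect monitoring, set the post assessment at the date the ten sessions were planned to end (10 sessions ÷ 5 per week = about 2 weeks from the first session), and the follow-up two months after that.

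Invite every randomised participant to both assessments, at least for the self-report primary scales (DRS, PI-WSUR, Y-BOCS). Record the number of sessions received and include these outcomes in the intention-to-treat analysis. Reconcile Participants and Adverse effect monitoring with Statistical analysis as to outcome assessment and inclusion in the analysis only. The treatment-stopping rules are not at issue and stay as they are.

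The cost is an amendment to the wording and some extra scheduling and contact effort. No new type of visit is needed, and Procedure already describes an online version of the self-report measures. Moving everyone to a strict calendar visit is unnecessary, and would mean assessing some late completers before their tenth session.

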**Fig. 1 Fig1:**
[figure not shown]
CONSORT flow chart

### Participants

Eligibility criteria include the following: aged 18–55 years; diagnosed with OCD based on The Diagnostic and Statistical Manual of Mental Disorders-Fifth Edition-Text Revision (DSM-V-TR) with significant contamination-based symptoms; sufficiently able to read, write, and do computerized tasks; being on stable medication for at least the last 3 months; and filling out the written consent.

The potential participants will be excluded if one or more of the following conditions are present: diagnosis of psychotic disorders or another comorbid with severe symptoms, alcoholism or drug abuse, a severe medical condition that may restrain the ability to engage in assessments and interventions, “Yes” answer to any items of screening questions for transcranial electric stimulation (tES) [43], invalid response on baseline tests.

Those participants who receive new medical prescriptions or other brain stimulations during the administering trial or follow-up durations will be excluded from further assessments or analysis.

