### Adverse effect monitoring

The stimulation protocol has been reported as safe and suitable for OCD symptom reduction in previous RCTs [39, 40], and there is no anticipated harm and compensation for trial participation. However, if a participant reports any moderate to serious problem, the stimulation will be stopped, and the trial will be discontinued for that participant, and if more than two participants report serious adverse events, the stimulation will be discontinued. According to the ethics committee rules, the trial management group is responsible for providing any necessary medical care due to trial participation.

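### Dropping randomised participants from assessment and analysis after a new prescription or other brain stimulation conflicts with the promised intention-to-treat analysis of all subjects

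*Protocol article*

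**What the plan says.** Three places in the protocol article bear on this point.

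- **Participants.** The rule covers those "who receive new medical prescriptions or other brain stimulations during the administering trial or follow-up durations will be excluded from further assessments or analysis". The trigger is any new prescription, not only a psychiatric one, and the window runs to the 2-month follow-up. This is separate from the entry requirement of "being on stable medication for at least the last 3 months".
- **Statistical analysis.** "We will conduct the analysis within the intention-to-treat (ITT) framework to investigate the effectiveness of the interventions for all subjects", and the sentence goes on to provide multiple imputation for missing data.
- **Adverse effect monitoring.** If a participant reports a moderate to serious problem, "the stimulation will be stopped, and the trial will be discontinued for that participant". The section does not say whether outcome assessments continue, and it does not mention analysis.

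The article attaches no per-protocol or sensitivity population to the exclusion, so it reads as a rule for the main analysis.

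**The concern.** An ITT analysis keeps every randomised participant in the arm assigned, whatever happens later. A rule that removes people for an event after randomisation replaces that population with one partly shaped by the course of the trial. Two analysts could each follow the article faithfully and analyse different sets of patients, and the choice could be made after the data are seen.

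There is also a reason to suspect that the event carries information. Participants enter on medication that has been stable for at least 3 months. For such patients a new psychotropic drug or another form of brain stimulation may well follow poor response, worsening or side effects, and any of these could differ by arm. This is an inference, because the article gives no reasons for such prescriptions.

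Because assessment stops as well as analysis, the later outcomes would be lost by design, and no later analysis could recover them.

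**Working it through.** **1. The two rules side by side.** Take a randomised participant who starts a new drug between the post-intervention visit and the 2-month follow-up.

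- Under Participants, this person is not assessed at 2 months and is excluded from analysis.
- Under Statistical analysis, this person is one of all the subjects analysed, with any missing value imputed.

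Both cannot be applied to the same analysis. One could read the word "further" as limiting the exclusion to later visits. That softens the conflict but does not remove it: the rule names analysis as well as assessments, and outcomes that could have been observed are still deliberately not collected.

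**2. What the plan's figures give.** The article has no figure for this exclusion. Its sample size does reproduce. For a repeated-measures MANOVA interaction with 4 groups, 3 time points, f = 0.40 and alpha 0.05:

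- s = min(4 − 1, 3 − 1) = 2 and df1 = 3 × 2 = 6
- df2 = 2 × (46 − 4 − 2 + 2) = 84
- noncentrality = 0.40² × 46 × 2 = 14.72
- power = 0.8015 at N = 46, the smallest N that reaches 0.80

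The enrolment target of 55 over four arms is 55/4 = 13.75 per arm, so two exclusions are 2/13.75 = 14.5% of an arm. The conflict in step 1 depends on none of these numbers.

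**3. Upper bound, one arm only (assumed).** Suppose a normal outcome with SD 1, and remove exactly the worst-scoring fraction p of one arm and nobody elsewhere. That arm's mean shifts by φ(z₁₋ₚ)/(1 − p):

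| p removed | φ(z) | shift (SD) |
|---|---|---|
| 0.05 | 0.103 | 0.103/0.95 = 0.11 |
| 0.10 | 0.175 | 0.175/0.90 = 0.19 |
| 0.15 | 0.233 | 0.233/0.85 = 0.27 |
| 0.20 | 0.280 | 0.280/0.80 = 0.35 |

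**4. A softer case, same rule in both arms (assumed).** The change score has SD 1 and lower is better. The exclusion probability is logistic, 1/(1 + exp(−(−2.5 + b × score))), with 400,000 simulated patients per arm.

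| True difference (SD) | b | Excluded, control / treated | Difference after exclusion (SD) |
|---|---|---|---|
| 0 | 1 | 10.5% / 10.6% | 0.00 |
| 0 | 1.5 | 13.7% / 13.8% | 0.00 |
| 0.40 | 0 | 7.6% / 7.6% | 0.40 |
| 0.40 | 1 | 10.6% / 7.6% | 0.38 |
| 0.40 | 1.5 | 13.8% / 8.9% | 0.35 |
| 0.80 | 0 | 7.6% / 7.7% | 0.80 |
| 0.80 | 1 | 10.6% / 5.3% | 0.76 |
| 0.80 | 1.5 | 13.8% / 5.6% | 0.71 |

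When exclusion is unrelated to outcome (b = 0) there is no bias. When it is related, a true 0.80 SD difference loses 0.04 to 0.09 SD, about 5 to 11% (0.04/0.80 to 0.09/0.80). With no true effect, nothing appears. Neither illustration credits any recovery through imputation.

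**The case against.** The best defence is that data collection simply stops at the event, earlier data stay in, and later values are imputed "for all subjects with multiple imputed data sets in case of missing data". That would be an ITT set with post-event data treated as missing. It is a debatable choice but a coherent one, and imputation can draw on each participant's baseline and earlier outcomes. This stands in part. It is a legitimate supplementary analysis, and it means one should not claim that imputation treats these patients exactly like completers. It does not rescue the text, which excludes them from analysis too. It also estimates what would have happened without the treatment change, which is a different question from the effect of assignment.

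A second objection is that letting co-treated patients stay in mixes new drugs into the follow-up scores of a trial interested in mechanism. That is fair, and it is a reason for a sensitivity analysis.

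A reader might also infer more than the article supports:

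- **That the rule selectively removes patients who do badly, mainly under sham.** The article gives no reasons for new prescriptions, and its wording also covers unrelated drugs.
- **That the Adverse effect monitoring section contradicts ITT.** It ends participation after a stimulation problem but removes nobody from the analysis. It is unclear, not contradictory.
- **That a large share of the planned effect would be hidden.** Such a share needs the one-arm worst case, ignores imputation, and requires converting a multivariate f of 0.40 into a single SD difference between arms, which the article does not support.

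**Conclusion.** The conflict between Participants and Statistical analysis is real and needs to be resolved, because it decides who is in the main analysis. It rests on the text alone and needs no assumption.

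The size of any bias is unknown. It depends on how many participants are excluded, and on whether exclusion is related to outcome and arm. The range runs from none (exclusion unrelated to outcome), through a loss of 0.04 to 0.09 SD from a true 0.80 SD (same outcome-related rule in both arms, about 11 to 14% of controls excluded), to a shift of 0.11 to 0.35 SD in one arm's mean (worst-scoring 5 to 20% of that arm alone). The last is an upper bound and not an expectation. The direction cannot be stated in advance: a common rule shrank the effect, while losses concentrated in one arm could shrink or inflate it depending on the arm.

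**What to change.** 1. **Participants.** Replace the exclusion sentence with wording such as: participants who start a new prescription or other brain stimulation after randomisation have the event and its date recorded, continue the post-intervention and 2-month assessments where they consent, and are analysed in the arm assigned.
2. **Statistical analysis.** State that the primary ITT analysis uses all observed data from all randomised participants, including data after such an event, with imputation for what is truly missing. As a sensitivity analysis, exclude these participants, or set their post-event data to missing and impute.
3. **Adverse effect monitoring.** Add that discontinuing a participant for a stimulation problem does not end outcome assessment, where the participant consents, and does not remove the person from the analysis. The clinical stopping rule itself is not touched.
4. **Reporting.** Give the number of such events by arm and their reasons.

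The cost is a change of wording and a few extra assessments in patients already enrolled. Some follow-up scores will reflect co-treatment, which the sensitivity analysis addresses. The article expected the last follow-up by the end of September 2023. If collection is over, outcomes that were not taken cannot be recovered, but the analysis rule can still be corrected and the affected participants kept in their assigned arms.
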